## Abstract

**Background:**

Yellow fever (YF) is a mosquito-borne and recently re-emerging viral haemorrhagic fever endemic to sub-Saharan Africa and South America. A highly effective vaccine against YF is licensed and recommended as part of routine childhood immunisation as a single dose at 9 months. Recent observational data demonstrate waning immunity following single primary vaccination and suggest that children in endemic areas may require booster vaccination.

**Methods:**

This open-label, non-randomised clinical vaccine trial (ClinicalTrials.gov, NCT05332197, registered on 31 March 2022, URL:
https://clinicaltrials.gov/study/NCT05332197) will assess the safety and immunogenicity of a booster dose of the licensed 17D YF vaccine in Gambian children. The trial will recruit 750 children in three cohorts of different ages (250 each). All children were vaccinated with the 17D YF vaccine at 9–10 months of age as part of clinical trials run by the Medical Research Council (MRC) Unit The Gambia, and are thus well-characterised, including basic clinical, anthropometric, and post-primary immunogenicity data. The children will receive booster doses at 15 months, 4 years, or 8.5 years. Serum samples will be taken before and 28 days after the booster, with additional sampling for exploratory endpoints in subgroups. Adverse events are solicited for the first three days following vaccination and recorded throughout the study period. The primary objective of the trial is to describe the safety and immunogenicity of the booster in the different age cohorts. Secondary objectives are to characterise the rate of sero-reversion (change from seropositive to seronegative) over a period of 9 months to 8 years following single primary vaccination and to profile the immune response to the booster to explore underlying mechanisms for the longevity of vaccine-induced antibody.

**Discussion:**

The results of this trial are likely to directly impact WHO recommendations on whether booster vaccination is required for children in endemic areas, and if so, the optimal timing of such a booster.

## Abbreviations

**AE**     Adverse Event

**AEFI**    Adverse Event Following Immunization

**CRF**    Case Report Form

**DMP**    Data Management Plan

**DSMB**    Data Safety and Monitoring Board

**ELISpot **   Enzyme-linked Immunosorbent Spot

**GCP**    Good Clinical Practice

**GMT**    Geometric Mean Titre

**ICH**    International Conference on Harmonization

**IEC**    Independent Ethics Committee

**MCA**    Medicines Control Agency, The Gambia

**MCV**    Measles-containing vaccine

**MRCG**   Medical Research Council Unit The Gambia at the London School of Hygiene & Tropical Medicine

**PBMC**   Peripheral blood mononuclear cell

**PI**   Principal Investigator

**PD**   Protocol deviation

**PRNT**   Plaque Reduction Neutralization Test

**RCD**   Reverse cumulative distribution

**SAE**   Serious Adverse Event

**SAGE**   Strategic Advisory Group of Experts

**SUSAR**   Suspected Unexpected Serious Adverse Reaction

**WHO**   World Health Organization

**YF**   Yellow Fever

## Introduction

### Background

Yellow fever (YF) virus is a mosquito-borne flavivirus found in Sub-Saharan Africa and tropical South America. The virus causes YF, a viral haemorrhagic fever, which can be prevented by a highly effective live-attenuated vaccine, however, it is now considered a re-emerging disease due to the increased numbers of cases in the last 30 years
^
1
^. Across Africa, 13 countries in West, Central and East Africa reported yellow fever cases in 2023 and 2024, with a case fatality rate of 11%
^
2
^. The median age of these cases was 25 years, with over two thirds of cases (69%) over the age of 15 years, suggesting a potential contribution of waning immunity to increased disease susceptibility
^
2
^.

In most endemic countries across sub-Saharan Africa and South America, the YF vaccine is administered alongside other Expanded Programme on Immunization (EPI) vaccines, including the first measles containing vaccine (MCV1), at nine to 12 months of age. Several recent publications from Africa and Brazil have raised doubts that a single dose of YF vaccine provides sufficiently long-lasting immunity. In a cohort of children vaccinated at around nine months of age in Ghana, seropositivity, measured by microneutralization assay, had fallen from an already low 73% at 28 days following primary vaccination to 28% at 2.3 years
^
3
^. This figure had increased to 43% by six years, perhaps as a result of natural exposure or unrecorded re-vaccination. Our own data from samples collected in The Gambia and Mali 6 years post primary YF vaccination administered via the routine EPI program showed that 22.2% of a cohort of 467 children had undetectable antibody concentrations, with another 7.5% revealing concentrations below the threshold of seropositivity of 0.5 IU/mL, confirming a substantial long-term decline in immunity
^
4
^. Cross-sectional studies in Brazil, including nine-month to 12-year olds, have similarly described a progressive decrease in the seropositivity rates from 87% within the first six-months after vaccination to 42% at six to eight years
^
5
^. A recent systematic review summarised the findings of 36 studies on over 17,000 participants aged 6 months to 85 years from 20 countries across the world, including Sub-Saharan Africa
^
6
^. In children vaccinated under the age of 2 years, the pooled seroprotection rate in a meta-analysis using a random effects model was 52% at 5 years following primary vaccination
^
6
^. In addition to waning immunity over time following primary vaccination, the co-administration of the YF vaccine with the first dose of MCV1 in many EPI programmes may contribute to a lack of protection, as a number of studies have shown that MCV1 co-administration interferes with the generation of YF immunity
^
7,
8
^. Concomitant infections and immunological interference from persistent maternal antibody may also contribute
^
9,
10
^.

It remains difficult to directly link the declining titres to actual occurrence of new cases of YF disease, as detailed immunisation history and in particular PRN titres are generally not available in observational studies of new cases, and no efficacy study has ever been performed. It is generally accepted, however, that high titres of YF antibodies protect against disease
^
11
^. Neutralising antibodies, in particular, are considered the primary mode of protection following YF vaccination and constitute the accepted correlate of protection for the disease
^
11
^. The low residual titres in young children are therefore a legitimate cause for concern
^
12
^. Our understanding of the role of cell-mediated immunity following YF vaccination is also advancing; although T-cell responses are believed to contribute to protection against disease, YF’s short incubation period underscores the importance of memory B cells and a rapid antibody response
^
11
^.

### Rationale

Despite the vaccine being very successful at decreasing disease risk, YF is considered a re-emerging disease due to the increased numbers of cases in the last 30 years. Until 2014, the vaccine was recommended to be administered with boosters every 10 years, but in 2014 the World Health Organization recommended removal of booster doses for all except special populations
^
13
^. This recommendation has been questioned and there have been reports of waning antibody titres in adults over time, and more recently also reports in paediatric populations. The scarcity of long-term studies on neutralising antibodies elicited in vaccinated infants has been identified as a knowledge gap with regard to the need for booster doses of the yellow fever vaccine
^
11,
14
^. Based on these emerging data, we need to establish whether infants who received a primary dose of a yellow fever vaccine at nine months of age, in line with EPI recommendations, are indeed likely to require a booster dose of the vaccine in order to ensure long-term protection.

We have a unique opportunity to address these questions of timing and immunogenicity which are of public health importance. The proposed trial leverages three well-characterized cohorts of infants in The Gambia, all of whom were vaccinated with the Institut Pasteur de Dakar 17D YF vaccine at nine to 10 months of age within clinical trials run at the MRC Unit The Gambia at the London School of Hygiene and Tropical Medicine (MRCG). Details of the vaccine lots used and other metadata, including anthropometric measurements and other health indices related to the infants at the time of vaccination, are available. These trials were all conducted with ethical approval at the MRC Unit in The Gambia and already have consent for future use of data and stored samples in the original informed consent documentation. For most children in these cohorts, the initial serological responses to the vaccine are already documented from assays previously conducted at the Robert Koch Institute in Berlin, and for others, serum samples from 28 days following the primary immunization remain in secure -80°C storage. At the time of the proposed study, the cohorts will range in age from between 15 and 18 months, to between eight and nine years. These cohorts therefore provide a unique opportunity not only to examine antibody decline over this time period, but also to determine the optimal timing of a booster dose following infant priming. In addition, they allow for comprehensive immune-profiling of innate and cellular responses to YF vaccination in the different age groups to generate new insights into determinants of long-term immunity. Such data have never been generated in paediatric populations.

## Study protocol (V2.0, July 2022)

This clinical trial protocol was registered on ClinicalTrials.gov on 31 March 2022 under registry number NCT05332197 and is available from
https://clinicaltrials.gov/study/NCT05332197
^
15
^.

### Study objectives

The main objective of this trial is to assess if a yellow fever (YF) booster dose is required for children who received a single dose of YF vaccination in infancy and if so, at what age this booster dose might be most effective to administer.

Primary:

To describe the safety and immunogenicity of a booster dose of a licensed YF vaccine administered to three different age cohorts of children, following a documented primary dose of a yellow fever vaccine administered at nine months of age.

Secondary:

To characterise the rate of YF PRNT seroreversion (seropositive to seronegative) over a period of 9 months to 8 years following a single primary dose of yellow fever vaccine administered to Gambian infants at nine months of age.To profile the immune response to the booster dose of YF vaccine in order to explore underlying mechanisms for longevity of vaccine-induced antibody.

### Potential risks and benefits

The risks are low as this is an already licensed vaccine and boosters have previously been recommended for adults with no safety concerns
^
16
^. The benefit is expected to be added protection against YF infection based on an increase in PRNT titres, the established correlate of protection. Participants may also benefit from being assessed by a study clinician at the time of enrolment. Should any health complaints be identified during this screening, initial treatment will be provided by the study team and the participant will be referred onwards for ongoing care, should this be necessary, at a government health facility.

### Study endpoints

Primary:

The primary endpoint of this study is the PRNT
_50_ titres post booster vaccination according to intervals between primary Yellow Fever vaccination and the booster dose.

Secondary:

The secondary endpoint is the rate of YF PRNT seroreversion (seropositive to seronegative) over a period of 9 months to 8 years following a single primary dose of YF vaccine administered to Gambian infants at nine months age.

Exploratory (Sub-study only):

Frequency of activated T cells, following re-stimulation with YF, in children of different ages following a booster dose of YF vaccinationLevels of YF specific memory B cells in children of different ages following a booster dose of YF vaccinationPossible impact of early innate responses, as measured by RNASeq, on antibody, B and T cell responses

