### Study design

This is a Phase 3 clinical trial to establish safety and immunogenicity of a booster dose of licensed YF vaccine in children of different age groups, following primary immunization with the same vaccine at 9–10 months of age.

The proposed study leverages three well-characterized cohorts of infants, all of whom were vaccinated with the Institut Pasteur de Dakar 17D YF vaccine at 9–10 months of age within clinical trials run by the Vaccines & Immunity Theme in the MRC Unit The Gambia at the London School of Hygiene and Tropical Medicine (MRCG) over the last few years (
Figure 1). The databases of the previous trials, the YF PRNT
_50_ results from the primary immunisation and the stored samples are immediately available to the investigators. Consent for sample storage and future work on remaining samples was obtained at the time of initial recruitment.

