### Selection and withdrawal of participants

**
*Selection of participants*
**

The study will recruit 750 healthy children to receive the booster dose of YF vaccine. A roughly equal number of boys and girls will be recruited. We do not expect there to be differences in the results by sex.

Participants will be recruited/ re-approached from the previously enrolled participants in each of the vaccine trials listed in
Table 1 below.

**Table 1. T1:** Cohorts to be re-approached as part of the trial.

Dates of 9-month yellow fever vaccination	Age in January 2022	Number of infants	Co-administered vaccines in original study	Serology in primary study	Study reference
Jul 2013 – May 2014	8 years 6 years	~1504	Combinations of IPV and measles and rubella	PRNT _50_	NCT01847872 SCC1327
Feb 2018 – Aug 2018	4 years	~675	Measles and rubella, OPV and PCV	PRNT _50_	NCT03197376 SCC1517
Dec 2020 – May 2022	9 months	~320	Measles and rubella, OPV and PCV	PRNT _50_	NCT03606096 SCC1600

Upon screening, potentially eligible children will continue until the end of study unless the trial is stopped for some reason. A child may be excluded from the trial for the purposes of vaccination and/or clinical sampling or if ongoing participation is considered to be against their best interests or if a contraindication to vaccination and/or to the obtaining of clinical samples is identified. Such decisions will be made by the PI in discussion with other members of the clinical trial team and/or the sponsor. A child excluded in this way would be replaced and hence this would not alter the target sample size of 750. If not enough children from the previous cohorts are available, we will aim to recruit appropriate age groups from community health centres. We expect this to be an exception rather than the rule.

**
*Eligibility of participants*
**

Participants must meet all of the inclusion criteria and none of the exclusion criteria to be eligible to participate in the trial. A representative sample of children will be recruited from the target population.

Inclusion criteria:

Any child fitting the required age cohorts who has a documented record of having received a primary dose of the Institut Pasteur YF 17D vaccine between 9 and 12 months of age. Documented evidence can be either a previous record of YF vaccination with dates in our own trial registers if the child was a previous participant or has documented evidence on its Infant Welfare Card.

Exclusion criteria:

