### Statistical considerations

**
*Sample size considerations*
**

The primary endpoint of this study is the PRNT titres post booster vaccination according to intervals between primary YF vaccination and the booster dose. A sample size of 250 participants per cohort provides a precision of around +/- 5% over a range of plausible seroconversion rates associated with boosting at the three different timepoints (
Table 3).

**Table 3. T3:** Precision around given estimates of seroconversion based on a sample size of 250 participants per group.

Seroconversion	95% confidence interval
95%	91.6 – 97.1
90%	85.7 – 93.1
80%	74.6 – 84.5
70%	64.1 – 75.3
60%	53.8 – 65.9
50%	43.9 – 56.2

The same sample size also provides over 80% power to detect a 10% difference in the seroconversion/seroreversion rates between two cohorts assuming a rate of at least 85% in one cohort, and over 90% power to detect a 15% difference in any two seroconversion/seroreversion rates.

Exploratory immunology sub-studies:

Our previous systems biology studies showed that significant differences in “omic” signatures over the first week of life and according to day of life were detectable in cohorts of infants as small as n=10 per group. We cannot currently confirm if such “omic” changes are informative to predict responses to YF vaccine in young children, but based on the data from Querec
*et al.*, systems biology approaches were informative in adults in group sizes as small as n=15
^
25
^. We are therefore confident that a group size of 30 per sub-group will provide us with sufficient datasets to not only explore if “omic” signatures in children are also predictive of humoral responses to the booster, but also to interrogate pathways and cellular populations involved in mediating correlates of protection against yellow fever.

**
*Data presentation and analysis*
**

Baseline data:

All baseline data including demographic and anthropological parameters will be tabulated by age cohort along with appropriate measures of spread. 

Immunogenicity data:

Descriptive evaluations including yellow fever PRNT GMT, seropositivity, seroreversion rates between 9 months and boost and seroconversion rates following boost (including the number of participants who seroconvert or who have a four-fold rise in antibodies concentrations) and relevant differences in these measures between age cohorts will be calculated and presented with appropriate measures of spread.

GMT data will be log

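### Post-booster titres are compared between cohorts without regard to response to the primary dose, so a difference read as an interval effect may partly reflect primary failure

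*Protocol article*

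**What the plan says.** Under Study endpoints, the primary endpoint is PRNT50 "titres post booster vaccination according to intervals between primary Yellow Fever vaccination and the booster dose". Eligibility requires a "documented record of having received a primary dose of the Institut Pasteur YF 17D vaccine between 9 and 12 months of age"; no response to that dose is required.

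Under Statistical considerations (Immunogenicity data), GMT, seropositivity, seroreversion and seroconversion are tabulated, and "relevant differences in these measures between age cohorts will be calculated and presented with appropriate measures of spread". The GMT ratio between cohorts is the back-transformed mean difference in log2 titre, with a two-sample t interval or a bootstrap interval if normality fails. No stratum or covariate is named.

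The data that would identify primary responders are held or planned. Study design says that the PRNT50 "results from the primary immunisation and the stored samples are immediately available to the investigators", and Laboratory investigations says that stored post-primary serum will be assayed where no result exists. In the immunogenicity analysis text, the only stated measure that depends on post-primary status is seroreversion, which starts from seropositive.

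**The concern.** The comparison is between three non-randomised cohorts, each drawn mainly from a different earlier trial, so anything that differs between those trials also differs with interval. Study objectives asks at what age a booster would work best, the rationale for participant selection speaks of the effect of the time interval, and the Discussion speaks of optimal timing. The cohort contrast will therefore be read as a timing effect.

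The protocol itself gives reasons to think that primary response is incomplete and may vary. Background reports a Ghanaian cohort in which seropositivity "had fallen from an already low 73% at 28 days following primary vaccination", and it says that measles vaccine given at the same visit interferes with yellow fever immunity. Table 1 shows combinations of IPV and measles-rubella for the oldest cohort, against measles-rubella, OPV and PCV for the other two. For a child with no detectable primary response, time since the dose may not mean the same as time since effective priming. If such children are more common in one cohort, its GMT can shift for a reason unrelated to interval, in a trial intended to inform booster policy.

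**Working it through.** **The plan's own figures.** The plan says: "A sample size of 250 participants per cohort provides a precision of around +/- 5"%, and "over 80% power to detect a 10% difference in the seroconversion/seroreversion rates between two cohorts assuming a rate of at least 85% in one cohort". Wilson score intervals with n = 250 reproduce all six rows of Table 3. With a two-sided 5% test (assumed, since the plan gives no level for power) and no continuity correction, 85% v 75% has 80.0% power. The lowest power for any 15-point difference is 92.1%, at 57.5% v 42.5%. These figures stand, but they concern proportions and do not bear on the composition of the GMT contrast.

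**Inputs for the check.**
- From the plan: 250 children per cohort, and an unadjusted comparison of mean log2 titre.
- Assumed, because the documents give no value: q1 and q2, the shares not seropositive after the primary dose in two cohorts; D, the difference in mean log2 post-booster titre between those children and primary responders; SD, the within-group standard deviation of log2 titre.
- No true interval effect within either group of children.

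**Formulas.**
- Shift in log2 GMT ratio: |q1 - q2| x D. The ratio is 2 to that power, or its inverse, since the sign of D is open.
- Variance in cohort i: SD² + qi(1 - qi)D². The second term is the extra spread from mixing two groups.
- SE = sqrt((V1 + V2)/250).
- False-positive rate = Φ(shift/SE - 1.96) + Φ(-shift/SE - 1.96).

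**One case in full (5% v 15%, D = 2, SD = 2).** Shift = 0.10 x 2 = 0.20, so the ratio is 2^0.20 = 1.15. V1 = 4 + 0.0475 x 4 = 4.19 and V2 = 4 + 0.1275 x 4 = 4.51. SE = sqrt(8.70/250) = 0.187. Shift/SE = 1.07, and the rate is 19%.

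| Shares | Ratio (D 2) | False positives (D 2, SD 2) | Range over D 1-3, SD 1.5-2.5 |
|---|---|---|---|
| Equal (5% v 5%, or 27% v 27%) | 1.00 | 5% | 1.00; 5% |
| 1% v 5% | 1.06 | 7% | 1.03-1.09; 5-14% |
| 5% v 15% | 1.15 | 19% | 1.07-1.23; 7-49% |
| 5% v 27% | 1.36 | 64% | 1.16-1.58; 16-98% |

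The 27% is 100% - 73% from the Ghanaian cohort and serves only as a high value.

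**Restricting to responders.** In this model the shift is then 0. The interval on the log2 scale widens by 1/sqrt(share responding): 1/sqrt(0.95) = 1.03 and 1/sqrt(0.73) = 1.17. The difference detectable with 80% power at SD 2, (1.96 + 0.84) x 2 x sqrt(2/n), rises from 0.50 log2 at n = 250 to 0.51 at n = 238 and 0.59 at n = 182.

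**The case against.** The strongest reply is that the primary objective is to describe immunogenicity in children with a documented primary dose. All once-vaccinated children are the right population for the policy question, and further analysis can go in the SAP, which is not shown. The first part stands: a reader might infer that pooling is itself an error, and it is not. The SAP argument stands only in part, because the endpoint and the form of the comparison are already fixed here and the objectives and Discussion read the contrast as timing. The rationale for participant selection does mention possible confounding factors, but only in general terms, and the stated comparison does not carry this through.

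Three stronger readings are tempting and not supported:
- *That a false interval effect is present.* It needs both unequal shares and different titres after the study dose. The documents show neither for these cohorts. Table 1 lists measles-rubella for all three, so interference from measles vaccine does not by itself imply unequal shares.
- *That the gap can be sized as 27% v 13% from the seropositivity figures of 73% and 87% in Background.* The first is a Ghanaian cohort measured by microneutralization at 28 days; the second comes from Brazilian cross-sectional studies within six months of vaccination. They differ in country, design and timing.
- *That a child below threshold at 28 days is unprimed, so that the booster is a first immunisation.* One low titre does not show this. The protocol describes T-cell and memory B-cell responses, and mentions natural exposure and unrecorded re-vaccination as possible.

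**Conclusion.** The concern holds in a limited, conditional form. The stated comparison takes no account of a pre-booster characteristic that is on file or will be measured, and that could differ by cohort. If it does differ, and titres differ with it, the unadjusted ratio is not a clean interval effect. The consequence runs from negligible (ratio 1.06 and about 7% false positives at 1% v 5%) to large (1.36 and about 64% at 5% v 27%), with D = 2 and SD = 2 assumed throughout. Because no non-response rate is given for these cohorts, none of these figures is a forecast. The all-children GMT remains a valid summary, and the sample-size figures are unaffected.

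**What to change.** - Keep the all-children GMT and GMT ratio as the primary, policy-facing summary.
- Pre-specify a between-cohort GMT ratio stratified by or adjusted for post-primary PRNT50 serostatus. The article reports follow-up complete and sample analysis under way, with the SAP due before database lock, so this should be fixed before results are seen.
- Base any statement about an interval effect on children seropositive after the primary dose, combining those who seroreverted with those still seropositive. Waning is part of the interval effect, so these two groups should not be separated for that contrast.
- Report children not seropositive after the primary dose separately, without calling them unprimed.
- Put children with no post-primary titre in their own category. The selection section allows recruits from community health centres, which does not fit the laboratory section's statement that post-primary serum is stored for all participants.

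The cost is SAP wording and extra tables, with no sampling beyond what is planned. The interval among responders is about 3-17% wider on the log scale if 73-95% responded (about 238 down to 182 of 250 children). The change removes this one source of cohort difference; other differences between the three source trials remain, and the report should say so.
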